# Processing of missing data

In this study, survival analysis was used to analyse the 1-year recurrence of atrial fibrillation for the primary efficacy endpoint. mITT and PPS were both included for the patients who failed to complete the 1-year follow-up due to half-way drop out or missing follow-up. The endpoint was defined as censored in the statistical analysis, and the censored date was the last follow-up date. No carry-over of missing data or multiple fillings of missing data were performed.

Missing data of secondary endpoints and safety endpoints, no filling or other processing is carried out.

Handling of dates: When only part of the date is known, the following rules are used to calculate the duration. If the start time (such as the date of first onset of AF or the date of diagnosis) is partially missing and only the day is missing, then fill in the first day of the corresponding month. If the end date is partially missing and only the day is missing, replace it with the last day of the month. If both the day and month of the date are missing, this date is treated as missing.

# Statistical analysis Methods

General principles of statistical analysis

Statisticians are responsible for developing a statistical analysis plan (SAP) with the principal investigator after the protocol is confirmed. Statistical analysis will be performed with SAS 9.4 (or higher version; SAS Institute, Cary, NC). The sample size is calculated using PASS13 software (NCSS, Kaysville, UT).

A 2-tailed P<0.05 will be considered statistically significant in all statistical tests. (If no other specification). No adjustments for multiple comparisons were made.

Qualitative data will be described with frequencies and percentages; quantitative data will be described with mean and standard error or with median and interquartile interval, minimum and maximum.

Continuous variables will be summarized with mean and SD and compared using paired t-test or Wilcoxon rank test, as appropriate. Categorical variables will be summarized with frequencies and percentages and compared using chi-square test or Fisher exact test, as appropriate. Ranked variables will be compared using Wilcoxon rank test or CMH test.

Enrolment Analysis

Enrollment analysis will summarize the number of enrollment and the number of subjects who completed the trial of each site and lists dropout subjects.

The dataset size between groups, subjects' disposition between sites, dropout rate and termination reasons will be listed in detail

Baseline and demographic characteristics

Baseline characteristics of patients will be described overall and per group.

Demographic and baseline characteristics (age, gender, height, BMI, vital signs, etc.), medical history, family history of atrial fibrillation, drug allergy, etc. of the subjects will be summarized. T-test or Wilcoxon rank-sum test will be used in baseline comparison of continuous variables such as age, height, and BMI between the two groups. The chi-square test or Fisher’s exact test will be used in the baseline comparison of categorical variables such as gender, and medical history

Analysis of efficacy

Both mITT and PPS were used for effectiveness analysis. Analysis performed on PP populations using the same methods can be considered as a sensitivity analysis.

(1) Baseline: The baseline of each relevant efficacy endpoints was described. For comparison methods between groups, refer to the general statistical method above.

(2) Primary efficacy endpoint: The recurrence rate of atrial fibrillation after ablation was statistically described in the two groups respectively.

Survival analysis was used to statistically analyse the recurrence rate of atrial fibrillation after ablation in the two groups. Kaplan-Meier curve of recurrence of atrial fibrillation after ablation was drawn between the two groups, and Log-rank test was used to compare the endpoint between the two groups. Besides, Cox proportional hazard regression model was used to calculate the risk ratio (HR) and 95% confidence interval (CI) of atrial fibrillation recurrence after ablation in the experimental group and the control group to estimate the efficacy, while considering each site as random effect included in the model.

- If atrial fibrillation recurred within 1 year, it was defined as the occurrence of end event. Time to recurrence of atrial fibrillation within 1 year=date of recurrence of atrial fibrillation-(date of radiofrequency ablation+90 days) +1, calculated by day.
- If the visit specified in the protocol was not completed within 1 year, the follow-up could not be completed by the end of 1 year due to loss of follow-up or withdrawal or other reasons, it was defined as censor, censor time=date of last follow-up-(date of radiofrequency ablation +90 days) +1, calculated in days.
- If the visit was completed within 1 year and no recurrence of atrial fibrillation occurred, it was defined as censor, and the censor time in analysis (1) was the date of last visit- (date of radiofrequency ablation+90 days) +1; The censor time in analysis (2) was 365 days.
- If the visits required by the protocol were completed within 1 year and AF recurred after 1 year, the endpoint was defined as event in analysis (1) and the recurrence time was the date of AF recurrence -(date of radiofrequency ablation+90 days) +1; the endpoint was defined as censor in analysis (2) and the censor time was the last visit- (date of radiofrequency ablation+90 days) +1.

(3) Secondary efficacy endpoints

Aimed at changes in atrial fibrillation load at 3 months, 6 months and 1 year after treatment, the mean, standard deviation, median, minimum, maximum, lower quartile (Q1) and upper quartile (Q3) of atrial fibrillation load at each visit site were calculated according to the form of quantitative endpoints. T-test or Wilcoxon rank sum test were used to compare it between the two groups. At the same time, the changes of atrial fibrillation load compared with baseline at 3 months, 6 months and 1 year after treatment were statistically described, and T-test or Wilcoxon rank sum test was used to compare the changes between the two groups.

The time of the first occurrence of atrial fibrillation/atrial fibrillation was analysed as the secondary endpoint. The occurrence days of atrial fibrillation/atrial fibrillation were calculated by the date of radiofrequency ablation surgery as the starting date, the occurrence days= the date of the first occurrence of atrial fibrillation/atrial fibrillation-the date of radiofrequency ablation surgery +1. For patients with atrial flutter/atrial fibrillation, the mean, standard deviation, median, minimum, maximum, lower quartile (Q1) and upper quartile (Q3) of occurrence time were calculated according to the form of quantitative variables. T-test or Wilcoxon rank sum test were used to compare the occurrence time between the two groups.

The secondary efficacy endpoint of transthoracic echocardiography one year after treatment were analysed. The indexes of transthoracic echocardiography mainly included left ventricular end-diastolic volume, left ventricular end-systolic volume, ejection fraction, stroke volume, cardiac output and other evaluation indexes. The mean, standard deviation, median, minimum, maximum, lower quartile (Q1) and upper quartile (Q3) of the results of the evaluation indicators were calculated according to the form of quantitative variables, and T-test or Wilcoxon rank sum test were used to compare the evaluation variables between the two groups.

The incidence of cardiac cardioversion within 1 year after treatment and the incidence of stroke and thromboembolism at 6 months and 1 year after treatment were analysed as secondary efficacy endpoints. The incidence and incidence difference of the two groups in the experimental group and the control group were described according to general principles. Meanwhile, Chi-square test or Fisher exact probability method were used to compare the incidence between the two groups.

SF-36 score within 1 year after treatment were analysed, and the mean, standard deviation, median, minimum, maximum, lower quartile (Q1) and upper quartile (Q3) of each dimension score were calculated according to the form of quantitative endpoints. And T-test or Wilcoxon rank sum test were used to compare the scores of each dimension between the two groups. It includes 8 dimensions and an overall score. The score of each dimension is calculated as follows:

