### Secondary efficacy endpoints

(1) Changes in atrial fibrillation load at 3 months, 6 months, and 1 year after treatment. Atrial fibrillation load was defined as the longest duration of atrial fibrillation episodes, the number of episodes of atrial fibrillation, and the percentage of time patients were in atrial fibrillation during a given monitoring period.

(2) Time of first occurrence of atrial flutter/atrial fibrillation.

(3) Incidence of electrical cardioversion within 1 year after treatment.

(4) Changes of transthoracic echocardiographic indexes at 1 year after treatment.

(5) Incidence of stroke and thromboembolism at 6 months and 1 year after treatment.

(6) Health Survey Summary Form (SF-36) score within 1 year after treatment.

Safety endpoints

(1) Adverse events (AEs): Any adverse medical events occurring between the time subjects signed the informed consent and were enrolled in the study and the last follow -up, regardless of whether there was a causal relationship with the study drug, was considered an adverse event. The sum of "definitely relevant", "possibly relevant" and "unascertainable" associated with the study drug was the adverse reactions (ADRs) of the study drug, and the incidence of adverse reaction was calculated accordingly.

(2) Laboratory indicators: blood routine, urine routine, stool routine, biochemical examination and coagulation function examination;

(3) Clinical physical examination and vitals.

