**Table 1: Summary Form of Health Status Survey (SF-36) scoring criteria**

| **8 dimensions + overall** | **Items** | **Scoring methods for each dimension** |
| --- | --- | --- |
| 1. Physiological Function(PF) | 3.1-3.10 | PF=[(actual score - 10) /20] x 100 |
| 2. Physiological Function(RP) | 4.1-4.4 | RP=[(actual score -4) /4] x 100 |
| 3. Body pain (BP) | 7,8 | BP=[(actual score -2) /9] x 100 |
| 4. Overall Health (GH) | 1, 11.1- 11.4 | GH=[(actual score -5) /20] x 100 |
| 5 Vitality (VT) | 9.1, 9.5, 9.7, 9.9 | VT=[(actual score -4) /20] x 100 |
| 6. Social Function (SF) | 6,10 | SF=[(actual score -2) /9] x 100 |
| 7. Emotional Function(RE) | 5.1-5.3 | RE=[(actual score -3) /3] x 100 |
| 8. Mental Health(MH) | 9.2, 9.3, 9.4, 9.6, 9.8 | MH=[(actual score -5) /25] x 100 |
| Overall: Health Change(HT) | 2 | HT=[(actual score - 1) /4] x 100 |

* Total Body Health measures (PCS) include: PF, RP, BP, GH;

* Total Measure of mental Health (MCS) includes: VT, SF, RE, MH.

* Scoring method for each dimension = (actual score - lowest score)/(highest score - lowest score)×100

* Actual score (for each dimension) = Add the scores for each item

Analysis of safety

Safety evaluation is analyzed on SS populations.

Proportion of antiarrhythmic drugs using within 90 days after radiofrequency ablation will be described in each group using frequencies and percentages. The range of antiarrhythmic drugs within 90 days after radiofrequency ablation was defined as the start date of ATC3 drugs between the day of radiofrequency ablation and the 90^th^ day of surgery.

Proportion of adverse events, severe adverse events, adverse reactions, and severe adverse events will be described in each group using frequencies and percentages. If necessary, changes of the laboratory and electrocardiogram variables will be analyzed before and after treatment.

Additional analysis

Additional analyses will be performed to compare primary and secondary endpoints between randomization groups after excluding patients who were still using antiarrhythmic drugs after 90days after radiofrequency ablation. Analysis methods for primary and secondary endpoints analysis described previously will be performed.

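### The SAP lets any of about 24 to 36 secondary tests, and the section 6.6 subset repeats, be called statistically significant at an unadjusted 0.05, with no ranking, gate or nominal label

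*SAP*

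**What the plan says.** Section 6.1 of the SAP fixes the threshold for the whole plan: "A 2-tailed P<0.05 will be considered statistically significant in all statistical tests. (If no other specification). No adjustments for multiple comparisons were made". The threshold is subject only to a different specification elsewhere, and none appears in the rest of the document.

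Section 3.1.2 lists six secondary efficacy endpoints. The first covers three time points, "Changes in atrial fibrillation load at 3 months, 6 months, and 1 year after treatment", and has three components: "Atrial fibrillation load was defined as the longest duration of atrial fibrillation episodes, the number of episodes of atrial fibrillation, and the percentage of time" spent in AF. Section 6.4 compares AF load between groups at each visit and then as change from baseline: "T-test or Wilcoxon rank sum test was used to compare the changes between the two groups". It also tests the time of first occurrence, five named echocardiographic indexes (the list is left open), cardioversion, and stroke and thromboembolism at two times. For SF-36, which has eight dimensions and an overall score, it states: "And T-test or Wilcoxon rank sum test were used to compare the scores of each dimension between the two groups".

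Section 6.6 then provides that "Additional analyses will be performed to compare primary and secondary endpoints between randomization groups after excluding patients who were still using antiarrhythmic drugs" beyond 90 days after ablation, using the same methods.

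Three statements bear on the standing of these analyses. Section 4 makes the mITT set primary. Section 6.4 says the per-protocol (PPS) analysis can be regarded as a sensitivity analysis. Section 3.1.1 defines two analyses of the primary endpoint. No section orders the secondary endpoints, names a key one, makes them conditional on the primary result, or describes their P values or those of section 6.6 as nominal, supportive or exploratory.

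**The concern.** Leaving secondary endpoints unadjusted is ordinary practice when their P values are presented as descriptive. Here the plan does the opposite: it gives every one of them the status of statistical significance at the full 0.05. An analyst who follows the SAP to the letter may therefore report significance for an AF-load measure, an echocardiographic index, an SF-36 dimension or a comparison in the section 6.6 subset, whatever the primary analysis shows.

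The section 6.6 subset is also selected on drug use after randomization, so it lacks the full protection of the random allocation. The plan gives its P values the same standing as those from the mITT set. Section 2.2 states the aim as high-quality evidence to guide drug use. A reader of the report could not tell, from the rule as written, which significant results carry confirmatory weight.

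**Working it through.** **The plan's own figure.** The SAP states no familywise error rate. Its only error-rate calculation is the sample size in section 2.5: 39.8% against 30%, 5% significance, 80% power. With unpooled variances, n = (1.960 + 0.842)² × (0.398 × 0.602 + 0.30 × 0.70) / 0.098² = 7.849 × 0.4496 / 0.009604 = 367.4, so 368 per group, as stated. Allowing for 20% loss, 368 / 0.80 = 460, also as stated. The sample size rests on the primary endpoint alone and is not affected by this point.

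**Count of secondary between-group tests (mITT set, one SF-36 time point).**

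| Endpoint | Tests |
| --- | --- |
| AF load: 3 measures × 3 times × (level and change) | 18 |
| Time of first occurrence | 1 |
| Echocardiography: named indexes only | 5 |
| Cardioversion | 1 |
| Stroke and thromboembolism: 2 times | 2 |
| SF-36: 8 dimensions and overall | 9 |
| **Total** | **36** |

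If AF load is read as a single measure, its row is 1 × 3 × 2 = 6 and the total is 24. With one test per listed endpoint the total is 6. The PPS and section 6.6 repeats are not counted.

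**Chance of at least one false P<0.05 when no secondary endpoint is affected.** For k independent tests this is 1 − 0.95^k:

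- k = 36: 1 − 0.95³⁶ = 84.2%, with 36 × 0.05 = 1.8 false positives expected.
- k = 24: 1 − 0.95²⁴ = 70.8%, with 1.2 expected.
- k = 6: 1 − 0.95⁶ = 26.5%, with 0.3 expected.

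The tests are correlated, and the SAP gives no correlations. For normal test statistics with an assumed common correlation ρ, the chance is 1 − ∫ [Φ((1.96 − √ρ·u)/√(1−ρ)) − Φ((−1.96 − √ρ·u)/√(1−ρ))]^k φ(u) du.

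| k | ρ = 0 | 0.3 | 0.5 | 0.8 | 0.9 |
| --- | --- | --- | --- | --- | --- |
| 36 | 84% | 72% | 55% | 27% | 18% |
| 24 | 71% | 59% | 46% | 24% | 16% |
| 6 | 26% | 24% | 21% | 14% | 11% |

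These figures count false benefit and false harm together. For false benefit only, the lower limit is dropped and the integrand becomes Φ((1.96 − √ρ·u)/√(1−ρ))^k. For k = 36 this gives 60% if independent, 38% at ρ = 0.3, 28% at 0.5 and 9% at 0.9. For k = 24 at 0.5 it is 23%.

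**A second correlation structure.** One common correlation across AF load, cardiac volumes, stroke and SF-36 is a simplification. With correlation within each domain and none between domains, simulation for 36 tests gives 74% when the assumed within-domain correlations are 0.5 (0.7 for the two stroke tests). It gives 51% when they are 0.8 to 0.9, and 44% if in addition the three cardioversion and stroke tests contribute nothing because events are rare.

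**If only part of the family is null.** If the drug truly affects the AF endpoints and only the 16 echocardiography, SF-36 and stroke tests are null, the chance is 56% if independent. It falls to between 51% and 38% at within-domain correlations of 0.3 to 0.7.

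**The case against.** The strongest defence is that the SAP is open about making no adjustment, names one primary endpoint and powers the trial only on it. Nowhere does it say that a secondary result can support an efficacy conclusion when the primary fails. Unadjusted secondary endpoints are common. All of that is fair. What remains is that openness about not adjusting does not settle how the results are to be described, and section 6.1 settles it as statistical significance for every test. If the protocol ranks the secondary endpoints, the SAP sentence would contradict it and would still need changing.

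Several stronger readings are tempting and should not be adopted:

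- A reader might infer that a false significant result is more likely than not. That requires every secondary null hypothesis to be true and only modest correlation. At a common correlation of 0.5 the figure is 55% for 36 tests but 46% for 24, and it is far lower at 0.8 or 0.9.
- A reader might take 36 as a minimum. Section 6.4 speaks of AF load as one quantity and does not say that its three components are tested separately, so 24 is a legitimate reading. Patients free of AF would score zero on all three components, which would also make those tests strongly correlated.
- A reader might say that no analysis is labelled supportive. The PPS analysis is called a sensitivity analysis.
- A reader might set the familywise figures against a promised 5%. The 5% in section 6.1 is a per-test threshold, and the SAP promises no familywise rate.
- A reader might say that a failed primary will be replaced by a chance secondary benefit. The plan permits such a claim but does not state that intention, and the chance of false benefit is about half the two-sided figure when tests are correlated.

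**Conclusion.** The concern holds as a fault in the decision rule. The plan grants full statistical significance at 0.05 to about 24 to 36 secondary tests, and again to the section 6.6 repeats, with nothing to separate them from the primary analysis.

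Its size can be given only as a range, because it rests on two assumptions: that the drug affects no secondary endpoint, and a correlation that the document does not supply. Under a common correlation from 0 to 0.9, the chance of at least one false significant result in either direction runs from 84% to 18% for 36 tests and from 71% to 16% for 24. Even with one test per endpoint and a correlation of 0.9 it is 11%. The existence of the fault does not depend on where in the range the truth lies. The primary comparison's sample size is unaffected.

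**What to change.** In section 6.1, replace the sentence that applies the threshold to all tests. State that a claim of statistical significance at two-sided 0.05 is made only for the primary efficacy analysis in the mITT set, and name which of the two analyses in section 3.1.1 carries it. State that secondary endpoints and the section 6.6 analyses are supportive, and that they are reported as between-group estimates with 95% CIs and nominal P values, without a claim of significance. The PPS analysis keeps its sensitivity label.

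If the sponsor wants a confirmatory secondary claim, a fixed testing sequence entered only after the primary succeeds is an option, with one measure and one time point per endpoint. It is not required.

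The change is to wording alone and needs no further patients or data. Its one small cost is that a nominally significant secondary result can no longer be presented as confirmed.

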### Inclusion Criteria

(1) Age 18-75 years old;

(2) Diagnosed with persistent atrial fibrillation;

(3) History of atrial fibrillation < 5 years;

(4) Radiofrequency ablation for the first time;

(5) Voluntarily participate in this study and have signed informed consent.

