### Exclusion criteria

(1) Valvular atrial fibrillation heart disease;

(2) NYHA cardiac function grade Ⅳ or LVEF<40%, LA diameter >50mm;

(3) Moderate to severe left ventricular hypertrophy (wall thickness >1.5cm);

(4) Patients with acute coronary syndrome or patients requiring stent implantation;

(5) Patients with a history of cardiac surgery and catheter ablation in the past 6 months;

(6) History of atrial fibrillation≥5 years;

(7) Hyperthyroidism;

(8) Patients with atrial fibrillation with cardiomyopathy;

(9) Patients with chronic arrhythmia requiring pacemaker installation;

(10) Patients with known bleeding constitution and left atrial/left auricular thrombus or severe hemostasis and coagulation dysfunction;

(11) Severe hepatic and renal insufficiency [ALT≥3 ULN or eGFR<50ml/min/1.7m^2^];

(12) Patients with neuropsychiatric diseases;

(13) Allergic to the ingredients of the study;

(14) Pregnant or lactating women;

(15) Patients who are participating in other clinical studies;

(16) Patients who are deemed unfit by the investigator to participate in this study.

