## Sample Size

Referred to《Catheter ablation vs. antiarrhythmic drug treatment of persistent atrial fibrillation: a multicentre, randomized, controlled trial (SARA study)》(European Heart Journal, 2014 Volume 35, Issue 8, Pages 501-507).

Assumed the 1-year recurrence rate of patients with persistent AF after radiofrequency ablation is 39.8% (the duration of an episode of AF/flutter/atrial tachycardia recorded by ECG≥30s 3 months after ablation is considered as a recurrence of AF). We predicted that the 1-year recurrence rate of atrial fibrillation could be reduced to 30% by adding Shensong Yangxin capsule after radiofrequency ablation. Therefore, we may expect that sample size of minimum 368 patients in each study group will provide the study with 80% power to detect a difference in primary outcome at 5% of significance. Accounting for 20% of lost to follow up patients of the trial, we need to include 460 patients in each group and the total sample size is 920.

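### The primary comparison pre-specifies no baseline covariate adjustment, although age, AF duration and left atrial diameter are assessed before randomisation: a modest missed efficiency, not an error

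*SAP*

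**What the plan says.** SAP section 6.4 (Analysis of efficacy), item (2), plans Kaplan-Meier curves and a log-rank test to compare the groups, with no strata or covariates named. In addition, a "Cox proportional hazard regression model was used to calculate the risk ratio (HR) and 95% confidence interval (CI"). Besides treatment, the only term named for that model is site, as a random effect. The per-protocol analysis reuses the same methods. The additional analysis in section 6.6 excludes patients still on antiarrhythmic drugs after 90 days and also reuses them. Neither is a covariate adjustment.

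Three baseline quantities must be assessed to decide eligibility:

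- age, limited to 18 to 75 years (section 2.4.1, item 1);
- AF duration: "History of atrial fibrillation < 5 years" (section 2.4.1);
- left atrial diameter: "LVEF<40%, LA diameter >50mm" are among the exclusions (section 2.4.2).

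Section 2.6 describes 1:1 block randomisation and names no stratification factor. Section 6.3 plans between-group tests of baseline characteristics but does not say what follows from them.

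The sample size (section 2.5) rests on unadjusted rates: "Assumed the 1-year recurrence rate of patients with persistent AF after radiofrequency ablation is 39.8" per cent, and "the 1-year recurrence rate of atrial fibrillation could be reduced to 30% by adding Shensong Yangxin capsule".

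**The concern.** In a time-to-event comparison, leaving out baseline variables that predict the outcome costs some power. The unadjusted hazard ratio is usually also a little nearer to 1 than the one conditional on those variables. If the groups happen to differ on such a variable, an unadjusted analysis makes no correction. With no adjusted analysis planned, any later adjustment would be post hoc and open to challenge. At stake are a little power for the main comparison and a clean answer to the reader who asks about imbalance. The validity of the primary result is not at stake.

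**Working it through.** **1. The plan's own figure.** Inputs from section 2.5: 39.8% versus 30%, 80% power, 5% significance. Section 6.1 makes the tests two-sided ("A 2-tailed P<0.05 will be considered statistically significant in all statistical tests").

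- Two proportions, unpooled variance: n = (1.960 + 0.842)² × (0.398 × 0.602 + 0.30 × 0.70) / 0.098² = 7.849 × 0.4496 / 0.009604 = 367.4, so 368 per arm. This matches "sample size of minimum 368 patients in each study group will provide the study with 80% power". The pooled form gives 371.
- Loss to follow-up: 368 / 0.80 = 460, as stated.
- Time-to-event check: HR = ln(0.70) / ln(0.602) = 0.703. Expected events with 368 per arm = 368 × (0.398 + 0.30) = 257. Schoenfeld's formula needs 253 events for 80% power; 257 give 80.7%.

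The unadjusted analysis therefore delivers its planned power.

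**2. What adjustment could add.** The SAP gives no prognostic strengths, so they are assumed over a range. Both simulations use exponential recurrence times with the marginal 1-year risks held at 39.8% and 30%, and Cox Wald tests of treatment without and with the covariates. The fitted models contain no site effect.

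Simulation A: 368 per arm, no dropout, one normally distributed prognostic score standing for all covariates combined, 4,000 trials per row.

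| Assumed HR per SD of combined score | Unadjusted power | Adjusted power | Gain (points) |
|---|---|---|---|
| 1.00 | 79.6% | 79.7% | 0.1 |
| 1.22 | 80.5% | 81.1% | 0.6 |
| 1.35 | 80.0% | 80.4% | 0.4 |
| 1.49 | 80.0% | 83.0% | 3.0 |
| 1.65 | 80.6% | 84.3% | 3.7 |
| 2.01 | 81.4% | 88.1% | 6.7 |
| 2.72 | 81.1% | 92.9% | 11.8 |

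Simulation error per power figure is about √(0.8 × 0.2 / 4000) = 0.6 points.

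Simulation B: 460 per arm with 20% uniform dropout, three independent covariates of equal strength, 2,000 trials per row. Their combined strength is exp(√3 × ln HR).

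| Assumed HR per SD, each covariate | Combined HR per SD | Unadjusted power | Adjusted power | Gain (points) |
|---|---|---|---|---|
| 1.2 | 1.37 | 85.6% | 87.2% | 1.6 |
| 1.3 | 1.58 | 85.5% | 88.0% | 2.5 |
| 1.4 | 1.79 | 85.9% | 90.2% | 4.3 |

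Simulation error here is about √(0.86 × 0.14 / 2000) = 0.8 points. At comparable combined strength the two simulations broadly agree.

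**3. Change in the hazard ratio.** In simulation A at 1.65 per SD, the average estimate is 0.700 unadjusted and 0.686 adjusted. These are two different quantities, marginal and conditional, and neither is wrong.

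**4. Chance imbalance.** With 460 per arm, the standard error of a standardised mean difference is √(2/460) = 0.066, so its 95% range is ±0.13 SD. An imbalance at that limit would shift the unadjusted HR by a factor of exp(0.13 × ln 1.35) = 1.04 to exp(0.13 × ln 1.65) = 1.07, about 4% to 7%.

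**5. Which test gains.** The only between-group test named is the log-rank test. Its P value does not depend on what is in the Cox model, so the gains above arise only if the adjusted Cox test becomes the primary test.

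**The case against.** The strongest reply is that nothing here is wrong. An unadjusted log-rank test with a Cox hazard ratio allowing for site is a legitimate pre-specified analysis. It matches a sample size built on unadjusted rates, and its confidence interval already allows for chance imbalance. That stands in full.

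Three further points also stand:

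- A reader might infer that the SAP ignores known prognostic factors. It never says that age, AF duration or left atrial diameter predict recurrence. An eligibility limit does not show it, since hyperthyroidism, wall thickness and renal function are restricted too. The limits also narrow the spread of these variables, which favours the lower part of the assumed range.
- A reader might infer that the Cox model costs the main comparison power. As written it does not, because the log-rank test makes that comparison.
- Meeting a threshold does not guarantee a usable continuous value for every patient. Section 5 expects partial AF onset or diagnosis dates and treats a date lacking both day and month as missing. A complete-case adjusted model could drop mITT patients and cancel a gain of a few points.

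Nor should much be made of the randomisation. The SAP names no stratification factor, but that detail may be in the protocol, which is not at hand.

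What the reply does not remove is that the SAP plans no adjusted analysis, even as a sensitivity analysis, and plans baseline tests with no stated consequence. In simulation A, adjusting for a score with no prognostic value cost nothing (79.6% versus 79.7%).

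**Conclusion.** The point holds as a missed efficiency worth taking up. The primary comparison uses no baseline covariate, although three candidates are assessed before randomisation. The likely gain is roughly 0 to 4 points of power for weak to moderate prognostic strength, and about 7 to 12 points only if the combined score is strong (HR per SD of 2.0 to 2.7). These figures rest on assumed strengths, exponential times and fitted models without a site effect; the SAP can confirm none of the strengths. The second benefit is a pre-specified answer to chance imbalance.

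The stronger conclusion, that the trial is underpowered or its primary analysis biased, is not supported: the planned 80% reproduces and the unadjusted hazard ratio validly estimates a marginal effect.

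**What to change.** In SAP section 6.4, item (2), before unblinding:

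1. Name as the primary test and hazard ratio those for treatment in a Cox model with treatment, a random site effect, and continuous baseline age, AF duration and left atrial diameter.
2. State that this hazard ratio is conditional on the covariates.
3. Add a simple rule for missing baseline covariates, for example imputing the overall mean without regard to treatment group, so that no mITT patient is dropped.
4. Keep the unadjusted log-rank test and unadjusted hazard ratio as supporting results.

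The cost is a few sentences. No new data should be needed, since these values are already assessed for eligibility. The downsides are an adjusted hazard ratio slightly different from the unadjusted one, and the need for the missing-covariate rule.
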